#### Data Collection and Follow-Up Phone Calls

Research assistants at each site will complete data collection from local medical records. For on-site participants and, where appropriate, for those assessed by telemedicine, they will compile the following information: age, sex, gender, ethnicity, postal code, distance from facility to home, referral by the provincial telephone consultation service (811, Telehealth), enrollment with a family physician, presenting complaints, comorbidities, regular medications, date and time of arrival and discharge, vital signs upon arrival, investigations and interventions during care episode, discharge diagnosis, and prescriptions upon discharge. A follow-up phone call will be made to all participants 10 days after the initial visit to collect data initially unavailable in medical records and to evaluate primary and secondary outcome metrics. Patient-reported outcome and cost measures will be completed by the participants at this moment, either on the phone with the research assistant or independently using a secured online survey link, depending on the participant’s preference. Text messaging and email reminders will be sent to improve participant retention [89]. We shall obtain information on health outcomes (eg, mortality) and physician charges via provincial databases. The charges billed by any physician 7 days after the initial visit will be used to estimate the costs of care for subsequent return visits and hospital admissions.

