#### The Costs

A prospective study in Ontario in 2005 [28] concluded that for similar cases, ED costs were 3 to 4 times higher than the costs incurred in a family physician’s office or a walk-in clinic. However, compared costs were not adjusted for comorbidities or severity of disease and did not include out-of-pocket expenses (eg, parking) and indirect costs to patients (eg, loss of income). Other studies, mainly from the United States, have reached similar conclusions [17,37-39] but using charges as proxies of health care costs, which has been shown to be an inaccurate costing method [40,41]. Some reports even suggest that walk-in clinics may in fact increase overall health care costs by duplicating care with frequent return visits after an initial visit [42-45].

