**Primary**			
	Incidence of return visit (O^a^)	Proportion of patients returning to any ED^b^ or outpatient clinic at 72 hours and 7 days after the initial visit [83,96-99]. An adjudication committee will review records of return visits to classify them as planned or unplanned and avoidable or unavoidable.	Follow-up call at 10 days
	Mean cost of care−the Ministry of Health perspective (C^c^)	The cost per care episode calculated by summing the costs of all care processes delivered to a patient during the initial visit plus the costs of return visits and admissions at 72 hours and 7 days.	Electronic medical records and provincial billing databases

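### The only stated cost source for return visits and admissions in the primary cost outcome is physician billing, while the initial visit is costed in full

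*Protocol article*

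**What the plan says.** Table 2 of the protocol article defines the primary cost outcome from "the Ministry of Health perspective" as the cost of all care processes "during the initial visit plus the costs of return visits and admissions at 72 hours and 7 days". Its listed source is "Electronic medical records and provincial billing databases".

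The two parts of that sum are costed in different ways.

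- **Initial visit.** Phase 1 (Design, Financial Data Sources, Intermediate Outputs of Phase 1) builds unit costs from staff time, consumables, overhead, traceable supplies and physician charges. In phase 2 each patient's visit is the sum of the standardized costs of what was received.
- **Return visits and admissions.** Data Collection and Follow-Up Phone Calls states: "We shall obtain information on health outcomes (eg, mortality) and physician charges via provincial databases". It continues that physician charges billed in the 7 days after the initial visit "will be used to estimate the costs of care for subsequent return visits and hospital admissions".

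Outcome Measures promises that costs to the health system or the patient over the following week will be added to the initial visit. Statistical Analysis says that return and admission costs are estimated separately and attributed to the setting of first presentation, and it names no unit cost. It also keeps a patient sent from a participating clinic to the ED, and then discharged home, in the clinic group, with the ED visit counted as a return visit.

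**The concern.** Physician fees are one part of the cost of an ED return visit or a hospital stay. Nursing, beds, overhead, tests and supplies are the rest, and from a public payer's view they belong in the outcome. If the follow-on part is built from billing data only, each return or admission is under-costed, and the total omitted grows with the number and intensity of those events. The protocol expects return rates to differ by setting, so the omission need not cancel in the comparison. The overlap weights, the balance checks and the E-value address confounding; none of them repairs a missing cost component.

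Adjusted cost is also one axis of the planned value graphic. The Introduction (The Costs) motivates the study partly by reports that return visits after walk-in care may raise overall costs. This is therefore a component on which the study question turns.

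**Working it through.** **1. What the document prices, and from what.**

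| Event | Physician part | Non-physician part |
|---|---|---|
| Initial visit, any setting | Phase 1 unit cost | Phase 1 unit costs |
| Return visit | Billed charges | No source stated |
| Admission | Billed charges | No source stated |

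The phase 1 list is averaged over 15 EDs, walk-in clinics and primary care practices. It could price an ambulatory return visit, but the document applies it to what the patient received during their visit and does not say that it extends to returns. It contains no inpatient price.

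**2. The protocol's own worked unit cost (Phase 1, Design).** Triage = duration × (nurse + consumables + overhead) = 7.1 × (0.78 + 0.07 + 0.17) = 7.1 × 1.02 = US $7.242, which reproduces the stated US $7.24. Its parts are nurse 5.538, consumables 0.497 and overhead 1.207. There is no physician term, so this step counts US $7.24 at an initial ED visit and US $0 at a return costed from physician charges. This shows the mechanism only. Triage is a nursing task, so it says nothing about the physician share of a whole visit.

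**3. One ED visit, two prices.** A patient who goes directly to the ED carries the full activity-based cost. A patient referred to the same ED from a participating clinic and sent home has that ED visit counted as a return, costed from physician charges.

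**4. Size of the possible shift.** Let r be the return rate in a setting and C the average non-physician cost omitted per return. The omission per enrolled patient is r × C. If C is the same in two settings, the contrast shifts by (r₁ − r₂) × C.

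Inputs from the document:
- Return rates of 1% to 13%, and a planned 72-hour difference of 5 points, for example 5% versus 10% (Sample Size).
- Pilot mean costs of US $59.8 in the ED and US $45.4 in primary care (Table 1), a difference of 59.8 − 45.4 = US $14.4. These are for upper respiratory tract infection only, from one ED and one clinic.

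C is not given, so it is solved for or assumed.

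Value of C at which the shift equals US $14.4:
- 5-point difference: 14.4 / 0.05 = US $288
- 12-point difference (1% versus 13%): 14.4 / 0.12 = US $120
- 1-point difference: 14.4 / 0.01 = US $1440

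Shift at a 5-point difference for assumed C:
- C = US $50: 0.05 × 50 = US $2.50
- C = US $200: 0.05 × 200 = US $10
- C = US $1000: 0.05 × 1000 = US $50

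The shift therefore runs from minor to larger than the pilot difference, depending on a figure that the document does not contain. Any admissions among the returns would raise the average C.

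**The case against.** The strongest reply is that the text does not say that charges are the only input. It says that they will be used to estimate these costs. Table 2 also lists medical records as a source, an adjudication committee will review records of return visits, and phase 1 yields a price list that could be applied to returns. On this reading, billing data identify the follow-on care and supply its physician component, and the rest is detail left to the full protocol or to appendices not shown.

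Part of this stands. Exclusive use of charges is an inference from the absence of any other named source, so a reader who concludes that nursing, bed and overhead costs are definitely left out goes further than the text. But the sentence is a stated method, not a silence. Records supply activities, not prices. Data collection is described from local records, whereas returns are counted at any ED or outpatient clinic. No inpatient price appears anywhere. If full costing is intended, the sentence misdescribes it.

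Three further inferences are tempting and not supported:

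- **That the bias favours clinics.** The Quality of Care section cites a study in which 72-hour returns were more likely after an ED episode than after other outpatient visits. The direction is open.
- **That the bias has a known size.** Assuming 1–2% admitted and US $3000–8000 omitted per admission gives 0.01 × 3000 = US $30 to 0.02 × 8000 = US $160 per patient. Both inputs are assumptions, and the result is an average omission. With equal admission rates and equal costs per admission in every setting, the contrast would not move.
- **That the protocol condemns its own method.** The Introduction faults other studies for "using charges as proxies of health care costs, which has been shown to be an inaccurate costing method". That concerns charges as a stand-in for total cost. Physician charges as one component are a deliberate part of this plan.

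**Conclusion.** The point holds as a defect in how a primary outcome is specified. As written, follow-on care is costed from physician billing and its non-physician costs have no stated source. That does not deliver the health-system scope in Outcome Measures or the Ministry of Health perspective in Table 2, and it gives one ED visit two prices.

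The consequence is conditional. If the sentence is followed literally, the setting with more returns or admissions looks cheaper than it is. The document does not allow that setting to be named or the error to be sized. The figures of US $288 and US $2.50 are illustrations. They assume the same omitted cost per return in both settings, apply the 72-hour planning difference to a cost that runs to 7 days, and use as yardstick a pilot contrast from one ED and one clinic for a single condition.

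**What to change.** Amend the sentence in Data Collection and Follow-Up Phone Calls, and align Table 2 and Statistical Analysis with it.

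- **Return visits.** Price each with the phase 1 standardized mean cost for the type of setting returned to. Use the billed charge either as the physician component or only to identify the visit. The phase 1 cost already contains physician charges, so state which applies and avoid counting the physician twice.
- **Admissions.** State a non-physician unit cost, for example length of stay from the provincial databases times a per-diem requested from hospital accounting, plus physician charges. Otherwise label this component as physician charges only and limit the cost conclusion accordingly.
- **Sensitivity analysis.** Report the charges-only version alongside.

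The cost is some added costing work, average prices for returns to non-participating sites, and one inpatient price that is not now in the plan and would have to be requested. It is best settled before the phase 2 data requests are made.

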#### Outcome Measures

A value-based comparative assessment requires the simultaneous evaluation of health outcomes and costs. Our outcome measures were chosen from a guideline on the assessment of ED performance [90] and recent literature on patient experience assessment (Table 2) [91-95]. The initial visit, from arrival at a participating site to discharge, represents the unit of analysis for all outcome measures; however, the health system or patient costs incurred during the following week will be estimated and added to the cost of the initial visit. For participants assessed in person, the outcome will be scored per care setting and further stratified per discharge diagnosis and by province, using institution-specific costs for interprovincial cost comparisons. We will analyze the same outcome measures separately in the case of patients evaluated by telemedicine, as missing data (eg, vital signs) will prevent us from adjusting for the severity of their illness.

**Table 2 table2:** Main study outcomes.

Outcome		Definition	Source
**Primary**			
	Incidence of return visit (O^a^)	Proportion of patients returning to any ED^b^ or outpatient clinic at 72 hours and 7 days after the initial visit [83,96-99]. An adjudication committee will review records of return visits to classify them as planned or unplanned and avoidable or unavoidable.	Follow-up call at 10 days
	Mean cost of care−the Ministry of Health perspective (C^c^)	The cost per care episode calculated by summing the costs of all care processes delivered to a patient during the initial visit plus the costs of return visits and admissions at 72 hours and 7 days.	Electronic medical records and provincial billing databases
**Secondary**			
	Median PROM-ED^d^ patients scores (O)	Developed and validated by team member SV, the PROM-ED questionnaire provides a measurement of patient-reported outcome expressed as scores for symptom relief, understanding of health concern, reassurance, and having a plan for care [91,94].	Follow-up call at 10 days
	Median scores on a PREM^e^ (O)	We adapted and are validating a tool from patient experience surveys used in EDs and primary care clinics in Ontario [100-102]. This tool evaluates the patient’s view of care delivery and measures various dimensions of patient experience relevant to all care alternatives, such as attitude of providers.	At the end of the initial visit
	Mean CoPaQ^f^ (C)	A questionnaire measuring patients’ and caregivers’ out-of-pocket expenses (eg, travel) and indirect costs (eg, loss of income) will be proposed to participants. This questionnaire was developed and validated by members of our team (ML, JG, SB) and further adapted for use in this study.	Follow-up call at 10 days
	Incidence of admission, intensive care unit, or mortality (O)	Proportion of patients who were admitted to the hospital or the intensive care unit or died because of one of the targeted respiratory conditions within 30 days [83,103] after the initial visit.	Provincial databases: Med-Echo, ICES, death registries
	Wait times	Median and mean length of stay and time spent waiting to see a physician.	Electronic medical records

^a^O: health outcome.

^b^ED: emergency department.

^c^C: health cost.

^d^PROM-ED: patient-reported outcome measure for ED.

^e^PREM: patient-reported experience measure.

^f^CoPaQ: cost-for-patient questionnaire.

To evaluate the quality of care in each group under study, compliance with practice guidelines (eg, corticosteroid prescription for asthma) for the treatment of respiratory diseases [104-109] will be compared (the full list of outcome measures is given in Multimedia Appendix 5 [83,91,94,96-103]). Return visits will be reported by the participants during the 10-day follow-up phone call. The Canadian Institutes of Health Research bridge grant obtained in April 2020 allowed our team to adapt questionnaires assessing patient perspective (Patient-Reported Experience Measure [PREM], patient-reported outcome measure for ED patients [PROM-ED], and cost-for-patient questionnaire [CoPaQ]) for use in any setting under evaluation. Their use for patients seen in person or by telemedicine in ambulatory patients with acute respiratory conditions will be validated further in the fall of 2020.

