#### Sample Size

As our main analyses focus on patients assessed in person, our sample size calculation is based solely on their numbers. We estimate that the rate of return visit for ambulatory emergency conditions varies from 1% to 13% depending on the care setting [17,110,111]. To account for the potential similarity in outcomes among individuals in each of the 15 clusters, we assumed a realistic intracluster correlation of =0.02 based on previous studies and applied a correction to inflate our sample size calculation [112,113]. Using data from Campbell et al [28], at least 1485 patients (approximately 99 per cluster) will be needed to reveal a 5% difference in the proportion of return visits within 72 hours (eg, 5% vs 10%), assuming a 20% loss to follow-up and at least 30 participants per condition, based on multivariate logistic regression power analysis, type I error (α) at .05, and power at 80% (1−β). Assuming 240 recruitment days over a year at each site and the recruitment of at least 1 to 2 patients per day, our final cohort should include over 4000 patients and reach the minimal sample size in both participating provinces, which will allow for more robust comparisons and analyses.

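### The primary return-visit outcome is taken only from participant report at day 10, while the billing data planned for costing the same visits are not used to identify them

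*Protocol article*

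**What the plan says.** Two primary outcomes are defined in Table 2 of the protocol article: the proportion of patients with a return visit to any emergency department or outpatient clinic, and the mean cost of care from the ministry's perspective. Both use windows of 72 hours and 7 days.

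- **Return visits.** The source column reads "Follow-up call at 10 days". The text after the table repeats this: "Return visits will be reported by the participants during the 10-day follow-up phone call". Table 2 adds a review step: "An adjudication committee will review records of return visits to classify them as planned or unplanned and avoidable or unavoidable".
- **Cost.** The source column lists electronic medical records and provincial billing databases. The section on data collection and follow-up calls says: "We shall obtain information on health outcomes (eg, mortality) and physician charges via provincial databases". It continues: "The charges billed by any physician 7 days after the initial visit will be used to estimate the costs of care for subsequent return visits"; hospital admissions are costed in the same way.
- **Loss.** The Sample Size section reaches 1485 patients "assuming a 20% loss to follow-up", for a 5-point difference (for example 5% against 10%) in return visits within 72 hours.
- **Use together.** The Statistical Analysis section plots adjusted cost against adjusted 72-hour return visits to show the value delivered by each site and setting.

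**The concern.** The plan measures the same event, a return visit within 7 days, in two ways. For cost, it is found through records and billing. For the return-visit proportion, it is found by asking the patient at day 10. The second route fails when the patient cannot be reached, forgets the visit, or places it on the wrong side of 72 hours. The first route does not need the patient to answer the phone.

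A visit can therefore be costed and not counted. The value graphic sets these two quantities against each other, so a setting could carry the cost of return visits that do not appear on its other axis. If reach or recall differed between settings, the primary comparison would be biased. If recall were equally incomplete everywhere, the differences would shrink.

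**Working it through.** **1. The plan's own figure.** 1485 was not reproduced from the stated inputs. For 5% against 10%, two-sided 0.05 and 80% power, the pooled two-proportion formula gives 435 per setting. That is 3 × 435 = 1305 before loss and 1632 after dividing by 0.8, with no allowance for clustering. The article cites a multivariate logistic regression power analysis whose inputs are not all shown. The present point does not depend on how 1485 was obtained; it is used below only as the planned number.

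**2. Patients with each primary outcome, at the planned size.**
- Return visits by call: 1485 × 0.8 = 1188, or 396 per setting if settings are equal.
- Not reached: 1485 − 1188 = 297.
- Cost by records and billing: up to 1485, or 495 per setting. Patients without provincial coverage are excluded (Selection of Participants), so all participants are insured by the province that holds the billing data.

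**3. Patients costed but not counted, from non-reach alone.** Assumed return rates among the 297:
- 5%: 297 × 0.05 = 14.9 patients
- 10%: 29.7 patients
- 15%: 44.6 patients

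Forgotten visits among the 1188 reached would add to these.

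**4. Effect on a rate.** True rate = 0.8 × observed rate + 0.2 × rate among the lost. With 5% observed:
- lost return at twice the rate (assumed): 0.8 × 5% + 0.2 × 10% = 6%
- lost return at three times the rate (assumed): 0.8 × 5% + 0.2 × 15% = 7%

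If this happened in one setting only, the error is 1 to 2 points against a 5-point target.

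**5. Effect on a difference.** Take observed rates of 5% and 10%, and let the true rate among the lost lie anywhere from 5% to 15% in each setting (assumed). The lower setting's true rate is 5% to 7%, and the higher setting's is 0.8 × 10% + 0.2 × (5% to 15%) = 9% to 11%. The true difference then lies between 9 − 7 = 2 and 11 − 5 = 6 points, around an observed 5.

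**6. Equal under-reporting.** If recall captured 80% of visits in every setting (assumed), 5% against 10% would be seen as 4% against 8%. Pairwise power at 396 per setting, ignoring clustering, would fall from 76.3% to 66.0%.

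**7. Power from more complete outcomes.** Going from 396 to 495 per setting raises pairwise power from 76.3% to 84.9% if clustering is ignored. With the stated intracluster correlation of 0.02, the design effects are 1 + 78.2 × 0.02 = 2.564 and 1 + 98 × 0.02 = 2.96, and power goes from 38.5% to 41.1%. The gain is therefore in completeness and consistency, and hardly in power.

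**The case against.** Several points on the other side have force.

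- **Reported visits are checked.** A committee reviews records of return visits, so dates and types of reported visits can be corrected. This stands. However, its stated task is classification, and nothing says it finds unreported visits or visits by patients not reached.
- **Other uses are not excluded.** The article says health outcomes will come from provincial databases and gives mortality as an example; the list is not closed, and the appendix with the full outcome list is not shown. This is fair, but for return visits the article names the call twice and no database.
- **Billing detail is not described.** The article does not say that charges carry location or hour, so billing cannot be assumed to settle the 72-hour boundary. This stands. The cost outcome, however, has the same 72-hour window, so those visits must be dated in some way already.
- **Billing is incomplete too.** A visit without a physician claim is seen only through the call, so some dependence on response remains. The Introduction also reports that outpatient notes often lack diagnosis and disposition, which limits classification for patients not reached. Both are reasons to combine the sources and not to demote the call.

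A reader might infer that loss will differ by setting, for instance because primary care patients are known to their practice. The documents do not support this: research assistants call all participants, with text and email reminders, under one procedure. Nor do they show that one patient in five is discarded. The 20% is a planning assumption, and the handling of missing outcomes may be in an analysis plan not shown. The article also expects over 4000 patients, which would leave about 3200 after 20% loss. That eases the concern about numbers, but not the one about which patients and events are counted.

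**Conclusion.** The concern holds as one of completeness and consistency between the two primary outcomes. As written, a return visit can enter cost without entering the return-visit proportion. Overlap weights balance measured confounders of the choice of setting; they do not repair an outcome that is missing or under-reported.

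The size and direction of any bias by setting are unknown. The 6% to 7% true rate, the 2-to-6-point range and the 80% recall figure rest on assumed ratios and are illustrations, not estimates. It would go too far to conclude that a 1-to-2-point bias is expected, that the billing data are already in hand (they are planned), or that adding them would rescue power. The study remains interpretable without the change, but a primary outcome has a weakness that data already in the plan can reduce.

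**What to change.** Reword the primary outcome so that a return visit at 72 hours and at 7 days is one identified by either provincial billing data or the day-10 call, in all consenting participants. Use service dates and retrieved records to date visits. Keep the call for visits without a physician claim, for the reason for the visit and to support adjudication. Report call-only and billing-only rates, and their agreement by setting, as sensitivity analyses. State the same event definition for the cost outcome, so that both axes of the value graphic count the same visits.

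The cost is wording and some analysis work. No new data source is needed, though the team should confirm that the planned extract carries service date and enough detail to recognise an emergency department or clinic visit. There are four downsides:
- billing data arrive with a lag;
- dating may be by day and not by hour, so a rule for the 72-hour boundary is needed;
- unbilled visits are still seen only through the call;
- classification of visits by patients not reached rests on records alone.
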